### Sample size {14}

The primary outcome is TTCI (censored at day 28). An interim analysis for futility and efficacy is planned at the midpoint of the trial. At this point the sample size may also be re-assessed. A one-sided type I error of 2.5% across the two stages of the trial and a power of 80% if the hazard ratio comparing remdesivir to placebo is 1.4 is used. This hazard ratio corresponds to a reduction in TTCI to 15 days on remdesivir if the TTCI on standard of care was 21 days. Triangular boundaries [16] are used to account for the multiple looks at the data, and allowance for the 2:1 randomization in favour of remdesivir is made. Under these assumptions, the total number of events required in this study is 325.

Assuming an 80% event rate within 28 days across both arms and a dropout rate of 10% implies that approximately 453 patients are to be recruited for this trial (151 on placebo and 302 on remdesivir).

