### Assignment of interventions: allocation

#### Sequence generation {16a}

A permuted block (30 patients per block) randomization sequence, including stratification, is prepared by a statistician not involved in the trial using SAS software, version 9.4 (SAS Institute). Patient randomization is stratified based on respiratory support methods at the time of enrolment: (1) no oxygen support, oxygen support with nasal duct or mask; (2) high-flow oxygen, NIV, IMV/ECMO.

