### Statistical methods

#### Statistical methods for primary and secondary outcomes {20a}

The primary outcome is TTCI up to day 28 of patients on remdesivir compared to patients receiving placebo. Patients will be randomized at a ratio of 2:1 to receive either remdesivir or placebo. All reporting will adhere to the Consolidated Standards of Reporting Trials (CONSORT) guideline as well as the corresponding extension for adaptive clinical trials [17, 18].

The final analysis of the primary endpoint will use a Cox proportional hazards model following the intention-to-treat principle. The final analysis will be conducted once a total of 325 events have occurred across both treatment groups. Under the assumption of an 80% event rate within 28 days and accounting for 10% dropout, this means that the maximum number of patients to be recruited is approximately 453. A standardized test statistic is then found on the basis of this model—if this test statistic exceeds 2.095, then it will be concluded that remdesivir is significantly better than placebo. Median unbiased effect estimates and confidence intervals accounting for the interim analysis will be reported [19]. Analysis of secondary endpoints will use a logistic model for binary variables such as mortality and a Cox proportional hazards model for time-to-event endpoints. A statistical analysis plan (SAP) providing all details of the analyses to be undertaken will be completed before any data analysis will be conducted.

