### 3.18.3. Methods for additional analyses (e.g. subgroup analyses) {20b}

Separate supporting analysis will be undertaken for gender and age groups (<60 and over 60 years of age at randomization). These analyses will use a Cox proportional hazards model of the primary endpoint. Additionally, mortality will be analysed for each of these subgroups using a logistic regression model.

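### The age subgroups leave out patients aged exactly 60, and the within-subgroup analyses come with no stated comparison between subgroups

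*Protocol article*

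**What the plan says.** All references are to the protocol article.

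- **Subgroups** (section 3.18.3): "Separate supporting analysis will be undertaken for gender and age groups". The two age groups are given as <60 and "over 60 years of age at randomization".
- **Models** (same section): for the primary endpoint, "These analyses will use a Cox proportional hazards model of the primary endpoint". For deaths, "mortality will be analysed for each of these subgroups using a logistic regression model". An interaction term is neither mentioned nor excluded. No significance level or rule for claiming a different effect is given.
- **Eligibility** (Eligibility criteria {10}): the lower age limit is 18 and there is no upper limit.
- **Details deferred** (Statistical methods {20a}): "A statistical analysis plan (SAP) providing all details of the analyses to be undertaken will be completed before any data analysis will be conducted".
- **Stratification** (Sequence generation {16a}): "Patient randomization is stratified based on respiratory support methods at the time of enrolment". This factor is not among the subgroups listed in section 3.18.3.

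**The concern.** There are two separate problems.

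**The age definition has a hole.** One group ends below 60 and the other is "over 60 years of age at randomization". Followed literally with age in completed years, the rule assigns a 60-year-old to neither. If this is noticed only after the data are seen, the side on which these patients fall becomes a post hoc choice.

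**No comparison between subgroups is stated.** One model per subgroup estimates the treatment effect in men, in women, in younger and in older patients. Whether two of those effects differ is another question, answered by their difference and its standard error. Where that comparison is not reported, readers tend to supply their own by noting which subgroup reached significance. With about half the events in each subgroup, that shortcut often suggests a difference where none exists.

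**Working it through.** **Inputs from the protocol** (Sample size {14}): hazard ratio (HR) 1.4, 325 events, 2:1 allocation, 80% event rate, 10% dropout, 453 patients.

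**Assumptions, not in the protocol:** the same true HR of 1.4 in both subgroups; events split 50/50, 60/40 or 70/30; two-sided 5% significance (critical value 1.96) in each subgroup; the trial runs to all 325 events; 1% to 4% of patients aged exactly 60 in completed years.

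**1. The plan's own figure.** 325/0.80 = 406.25, rounded up to 407. 407/0.90 = 452.2, rounded up to 453. Split 2:1, this is 302 and 151. The stated sample size reproduces. The protocol gives no figure for the subgroups.

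**2. Age gap.** 453 × 0.01 = 4.5 and 453 × 0.04 = 18.1, so about 5 to 18 patients. In events, 325 × 0.01 = 3.25 and 325 × 0.04 = 13, so about 3 to 13.

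**3. Power within one subgroup.** With d events and 2:1 allocation, the information on the log HR is d × (2/3) × (1/3) = d × 2/9. Power = Φ(ln 1.4 × √(d × 2/9) − 1.96), with ln 1.4 = 0.3365. For half the events, d = 162.5: √36.11 = 6.009, 0.3365 × 6.009 = 2.022, and Φ(0.062) = 0.525.

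**4. Exactly one of the pair significant, with no true difference.** With powers a and b, the probability is a(1 − b) + b(1 − a).

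**5. At least one estimate reversed (HR below 1).** For one subgroup the probability is Φ(−ln 1.4 × √(d × 2/9)). For the pair it is one minus the product of the complements.

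| Split | Events | Power in each | Exactly one significant | At least one reversed |
|---|---|---|---|---|
| 50/50 | 162.5 / 162.5 | 52.5% / 52.5% | 2 × 0.525 × 0.475 = 49.9% | 4.3% |
| 60/40 | 195 / 130 | 60.1% / 44.0% | 0.601 × 0.560 + 0.440 × 0.399 = 51.2% | 4.8% |
| 70/30 | 227.5 / 97.5 | 66.7% / 34.7% | 0.667 × 0.653 + 0.347 × 0.333 = 55.1% | 6.7% |

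**6. What an interaction test would do.** The standard error of the difference in log HRs is √(1/I₁ + 1/I₂), with I = d × 2/9 in each subgroup. At 50/50 this is √(2/36.11) = 0.235. Power for a ratio of HRs of 1.4 is Φ(0.3365/0.235 − 1.96) = 29.8%. It is 28.8% at 60/40 and 25.9% at 70/30. The ratio detectable with 80% power is exp(2.80 × SE), which gives 1.93, 1.96 and 2.05. False claims of a difference are held to 5% per factor, or 1 − 0.95² = 9.75% for two factors if independent.

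**The case against.** The strongest objection is that this is a condensed article that defers all analysis details to an SAP that is not shown. Interaction terms and the reporting format for subgroups are commonly left to that document. The analyses are called supporting and carry no threshold or claim. Separate fits also give hazard ratios with confidence intervals, which is largely what a reader needs. The word for separate could mean separate from the primary analysis.

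Much of this stands, and it rules out several stronger readings that a reader might infer:

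- **That subgroup effects will be judged by significance in each model.** The text sets no such rule. The 50% to 55% figure applies only if someone reads the results that way.
- **That an interaction test has been left out.** Section 3.18.3 does not exclude one, and the SAP may contain it.
- **That the age gap makes conflicting subgroup results likely.** Dropping a few patients aged 60 does not produce conflict. The two problems are unrelated.
- **That effects in opposite directions are likely.** Under the same assumptions they occur in only about 4% to 7% of trials.
- **That respiratory support must be a subgroup.** Stratifying randomisation on a factor creates no such obligation, and the protocol gives no reason for the stratification from which one could be argued.

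Two things survive. The age cut is wrong as written, whatever the SAP adds. And the mortality sentence, which refers to each of the subgroups, points to within-subgroup models; these need a comparison between subgroups before they can say anything about a differing effect.

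**Conclusion.** The point holds and is minor. The age definition is an error in the protocol's own text. It affects about 5 to 18 of 453 patients if 1% to 4% are aged exactly 60. The protocol gives no age distribution and does not say how age is recorded, so that range is an assumption. The primary analysis is untouched.

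On the models, the conclusion is conditional. The described analyses do not show whether the effect differs between subgroups. Read by significance, they would suggest a difference in about 50% to 55% of trials when the true HR is 1.4 in both subgroups. This rests on the assumed splits and two-sided 5% tests, although the figure moves little between 50/50 and 70/30.

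**What to change.** 1. Define the age groups as <60 and ≥60 years at randomisation.
2. Unless the SAP already does so, fit one Cox model per factor for time to clinical improvement, and one logistic model per factor for mortality, each with a treatment-by-subgroup term. Report each subgroup's estimate with its confidence interval, together with the interaction result.
3. State that a non-significant interaction will not be read as proof of a uniform effect, because power is only about 26% to 30% for a ratio of HRs of 1.4.

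A respiratory-support subgroup may be added but is optional.

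The cost is a change of wording. It needs no new data or patients and leaves the primary analysis as it is. The drawback is the low power of the interaction test: it limits false claims of a difference but would miss most real differences of that size.

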### 3.18.4. Methods in analysis to handle protocol non-adherence and any statistical methods to handle missing data {20c}

Multiple imputation will be used for missing data. The primary analysis will use the intention-to-treat principle and a per protocol analysis will be undertaken to assess the robustness of the findings.

### 3.18.5. Plans to give access to the full protocol, participant-level data, and statistical code {31c}

These plans are not yet in place.

#### Trial monitoring

Trial monitoring is performed by Hangzhou Tigermed Consulting Co., Ltd.

#### Data management team

The data management team is Hangzhou Tigermed Consulting Co., Ltd.

#### Clinical research organization

The clinical research organization is Hangzhou Tigermed Consulting Co., Ltd.

### Composition of the data monitoring committee, its role and reporting structure {21a}

The independent Data Safety Monitoring Board (DSMB) in this study is responsible for reviewing the reports regarding the safety of the study patients and protocol adherence and making recommendations to continue or terminate the study or modify sample size on the basis of the results from the interim analysis. The DSMB members are all independent of the sponsor and have no financial or other conflicts of interest.

### Adverse event reporting and harms {22}

AEs and SAEs will be collected from the time of informed consent to day 28. SAEs occurring after day 28 ± 3 will be reported if investigators determine that these SAEs are related to the study drugs. SAEs will be followed up until the SAE has subsided, returned to baseline, or is stable.

Investigators or designees are responsible for collecting, assessing, reporting, and managing AEs. AEs will be fully investigated and recorded in detail in the CRF, including onset date, the duration of AE, symptoms/signs, severity, action taken to manage the AE, relationship with the study drug, outcome of the AE, and date of outcome assessment (if outcome was other than recovering, not recovered, or unknown).

### Frequency and plans for auditing trial conduct {23}

The contract research organization (Hangzhou Tigermed Consulting Co., Ltd.) will be responsible for monitoring the trial. On-site monitoring and remote monitoring visits will be conducted in accordance with the study monitoring plan to ensure the completeness and accuracy of research data. Audits may be conducted at any time during or after the study.

### Plans for communicating important protocol amendments to relevant parties (e.g. trial participants, ethical committees) {25}

During the trial, the principal investigator will inform the Independent Ethics Committee (IEC) of any revision or modification of the protocol. The revision or modification will only be implemented after receiving IEC approval, unless it is necessary to be implemented in order to eliminate immediate and direct harm to patients, in which case the IEC will be informed as soon as possible.

After any protocol amendment, the informed consent form and any other written information provided to subjects will be updated as necessary. Investigators will inform subjects in time and ask them to sign the revised informed consent form to confirm their participation. The updated informed consent form must be approved by the IEC before implementation.

### Dissemination plans {31a}

We will communicate trial results to national and international health authorities, healthcare professionals, the public, and other relevant groups as soon as the trial results are available.

## Discussion

This study is the first double-blind, placebo-controlled trial of an experimental therapeutic for COVID-19. Whilst the COVID-19 epidemic has been declared a public health emergency of international concern, this does not negate the need to generate robust evidence in which healthcare professionals, patients, their families, and public health authorities can have confidence. In past epidemics, unproven treatments have been used on a compassionate use basis, in observational studies, or in underpowered trials, and the results are uncertainty and ongoing treatment dilemmas. Randomized, placebo-controlled trials are well established as the best way to minimize bias and confounding and produce reliable evidence. Such trials can be implemented even in the most difficult circumstances; in fact, the difficult circumstances themselves make it even more important that patient care is not driven by fear and rumour but by science and evidence. During health emergencies, doctors and politicians are under enormous pressure to find cures to save lives and stop the epidemic, whilst patients are willing to try anything in the face of a frightening and unknown threat. We must resist these pressures and make sure that patients benefit from the fruits of science, even in difficult times.

The use of placebo is especially beneficial in the midst of great anxiety, when the pressures to announce a cure or act on preliminary, but inconclusive data, are intense. A placebo relieves the temptation from all involved in the trial to engage in speculation and the worry that they are withholding what early (but often false) impressions may suggest is a promising drug. Whilst remdesivir has shown promising activity in preclinical models of severe CoV infection, it is currently unknown whether it will prove safe and effective in treating severe COVID-19, both because of its uncertain antiviral efficacy and the unclear importance of ongoing viral replication versus an inflammatory process in disease pathogenesis in severely ill patients. Of note, remdesivir yielded positive results in preclinical models of Ebola virus infection but was inferior to two monoclonal antibody therapies in treated patients [15].

During epidemics, as well as calls to treat everyone, other voices demand that vulnerable patients not be treated as ‘guinea pigs’. Clinical trials use well-deliberated, tested, and transparent scientific methods, and are undertaken as a joint endeavour between patients and health professionals within a clear ethical framework. Health emergencies raise additional ethical concerns, but these have been carefully considered by various groups, and clear guidance exists on the conduct of clinical research during health emergencies [20–22].

The choice of the primary endpoint for a clinical trial is always challenging, but it has added difficulties when dealing with a disease with uncertain natural history, an overstretched workforce, and the desire for an early answer. This requires an endpoint that is clinically meaningful, is based on simple data collection, has sufficient power, and will occur early. It also requires statistical methods that are robust to misspecification of design parameters, such as the endpoint frequency. We believe that our primary endpoint is both pragmatic and informative, but we have included a range of secondary endpoints to show consistency with the primary endpoint, as recommended by the US Food and Drug Administration for trials in influenza [23].

### Trial status

The protocol version is number 3.0, dated 9^th^ February 2020.

The first patient, first visit was on 6^th^ February 2020; the recruitment end date was anticipated to be 3^rd^ April 2020.
